#### Interim analyses {21b}

We do not plan to perform an interim analysis.

#### Methods for additional analyses (e.g., subgroup analyses) {20b}

No additional analyses are planned.

#### Methods in analysis to handle protocol non-adherence and any statistical methods to handle missing data {20c}

No missing data will be accepted for the primary end-point. If there are no measures of pain relief after the postoperative day three registered, but the diary is completed, the TOTPAR will be considered as 100% starting from the next blank page. In a case of missing data for the first three days post-discharge, patients will be replaced by new patients, recruited up to 186-target accrual. Missing data for the secondary endpoints will be examined and the decision guided by a principal investigator and statistician will determine whether these data will be excluded or imputed. In that case, a Multiple Imputation by Chained Equations (MICE) will be performed. A R-software implemented algorithm imputes missing data through an iterative series of predictive models using the other existing variables in the dataset.

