### Objectives {7}

We hypothesize that an educational intervention based on the rational perception of postoperative pain and discomfort, and the proper use of analgesics would improve the quality of pain management at home and reduce analgesics-related side effects.

The study evaluates the effectiveness of an educational intervention on pain relief at home in outpatient orthopedic surgery, compared to standard care. The pain relief is assessed during the first five post-discharge days (primary outcome), then on the 10th, 20th and 30th days after surgery (secondary outcome). The prevalence of severe pain (as reported by participants), medication use, side effect of medication, changes in sleep quality, the incidence of neuropathic pain at day 30 after surgery, and overall satisfaction at day 30 will be assessed as a part of secondary objectives.

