### Outcomes {12}

The primary outcome is the pain relief measured with a percentage of maximum total pain relief (TOTPAR) over 5 days. TOTPAR is a time-weighted measure of total area under the pain relief curve. This measurement assimilates iterative assessments of a subject’s pain over the duration of the study.

The secondary outcome includes:TOTPAR at day 10, day 20, and day 30 after surgeryThe incidence of severe pain (defined as “severe pain” by the patient)Type, quantity, and doses of taken analgesicsNeuropathic pain prevalence at day 30, detected with DN4 scale [38]The sleep quality measured with Pittsburgh Sleep Quality Index (PSQI) [39] and compared at inclusion day and at the 30th postoperative dayPatients’ perception of postoperative pain management evaluated at with the International Pain Outcome (IPO) questionnaire [40] on day 30 after surgery

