### Assignment of interventions: blinding

#### Who will be blinded {17a}

Due to the nature of the intervention, the allocation cannot be masked neither for participants nor for physicians or data managers

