#### Plans to promote participant retention and complete follow-up {18b}

After the inclusion and discharge from the hospital, patients receive a short text message and/or e-mail reminders to complete the follow-up on days 0, 1, 2, 3, 4, 5, 10, 20, and 30 post-discharge. A postal stationery envelope (prepayment of postage) with the printed investigator’s return address is given to each patient along with the diary. Patients are invited to return their diary via the post service, or they may bring it to the hospital. Two weeks following the end of study, if there is no diary return, the patient is contacted by the associate research coordinator and invited to send the diary to the investigator.

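### Blank day 4–5 pages in a completed diary are scored as full pain relief, a best-case fill of up to 40% of the primary score

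*Protocol article*

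**What the plan says.** Under Outcomes {12}: "The primary outcome is the pain relief measured with a percentage of maximum total pain relief (TOTPAR) over 5 days". The same section describes the measure: "TOTPAR is a time-weighted measure of total area under the pain relief curve". Objectives {7} sets the window as the first five post-discharge days.

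The missing-data section {20c} opens by saying that missing data are not accepted for the primary endpoint. It then gives the rule at issue. The condition is "If there are no measures of pain relief after the postoperative day three registered, but the diary is completed", and the consequence is "the TOTPAR will be considered as 100% starting from the next blank page". Patients with missing data in the first three days are replaced. Secondary endpoints have a separate rule: their missing data are examined and then excluded or imputed with MICE.

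On masking, section {17a} says that "the allocation cannot be masked neither for participants nor for physicians or data managers". Section {20b} plans no additional analyses.

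**The concern.** A blank page is the absence of a measurement. It may mean that pain has gone, but it may also mean fatigue with a diary on a 30-minute grid, forgetting, or a bad day. The rule gives all of these the best possible value, with no uncertainty attached. The article gives no reason for equating a blank with full relief and no way to verify it. Because completed is undefined, someone must judge which diaries qualify, and physicians and data managers know the allocation.

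Two things are at stake. If blank pages are more common in one arm, that arm's primary score rises for reasons unrelated to pain. If they are equally common, both arms move toward the ceiling and a true difference shrinks somewhat.

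**Working it through.** **The plan's own figure.** The article gives no figure for the share of the endpoint open to this rule. The sample size does reproduce and supplies the arm size used below. With 30% vs 17.6%, two-sided 5%, 80% power and pooled variance under the null:

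n = [1.960 × √(2 × 0.238 × 0.762) + 0.842 × √(0.210 + 0.145)]² / 0.124² ≈ 184 per arm, 368 in total, as stated in {14}.

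**Share of the primary score.** TOTPAR is time-weighted, so each full day carries equal weight. Gaps in the first three days lead to replacement, so within the primary window the rule reaches days 4 and 5.
- Days 1–5 ({7}, {12}): 2/5 = 40%.
- Days 0–5, if the day 0 diary page counts (Table 1, {18b}): 2/6 = 33%.
- Only day 5 blank, if the rule is read to cover that case: 1/5 = 20%.

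**Gain for one affected patient.** Gain = share × (100 − R), where R is true mean relief on days 4–5. R is not in the documents.

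| Assumed R | Gain, 5-day window | Gain, 6-day window |
|---|---|---|
| 60 | 0.4 × 40 = 16 | 13.3 |
| 70 | 0.4 × 30 = 12 | 10.0 |
| 80 | 0.4 × 20 = 8 | 6.7 |
| 90 | 0.4 × 10 = 4 | 3.3 |

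**Bias between arms.** With no true effect, and the same R among blank patients in both arms, bias = (difference in blank rates) × 0.4 × (100 − R). At R = 60, a 10-point difference in blank rates gives 0.10 × 16 = 1.6 points and a 20-point difference gives 3.2. At R = 80 these are 0.8 and 1.6. Equal rates give zero.

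**Type I error.** Simulation with no true effect, Mann-Whitney at 0.05 (the test named in {20a}) and 184 per arm. Assumed inputs: daily SD 25, within-patient correlation 0.6, scores clipped to 0–100. Repeat runs differ by about one percentage point.

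| Relief pattern and who leaves pages blank | Blanks 20% vs 30% | Blanks 10% vs 30% |
|---|---|---|
| Flat 60%, blanks unrelated to pain | about 12% | about 39% |
| Rising 60/65/70/85/90, blanks unrelated to pain | about 7% | about 11% |
| Flat 60%, blanks in patients with most relief | about 5% | about 9% |
| Rising, blanks in patients with most relief | about 5% | about 4% |

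Equal blank rates (20% in both arms, unrelated to pain) give about 5%. With equal blanks of 0, 20% and 40%, power for a true difference of about 6 points falls from about 84% to about 79% and 75%.

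**The case against.** The strongest defence is that the rule is narrow, prespecified and identical in both arms. It excludes unreturned diaries and patients with gaps in days 1–3. What remains is patients who recorded the first three days and then stopped, and some of them will have stopped because pain had gone. The article places the main problem in the first 72 hours, so relief on days 4–5 may well be high, which makes the fill nearly right and the bias small. Imputing from days 0–3 could then understate relief. This stands as a limit on the size of the problem and as a real cost of the remedy. It does not justify scoring every such blank at the ceiling without a check.

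It also stands that the documents do not show unequal blank rates. The diaries are described as differing only in the scale on page one and the narration on page two. Sections {11c} and {18b} describe the same reminders for both arms, although Table 1 marks none on days 2–4. Unequal blanking is plausible because patients know their allocation and the intervention aims to change how they judge pain, but that is inference.

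The full protocol and any SAP are not shown and may contain sensitivity analyses; the statement in {20b} stands under a heading on subgroup-type analyses. The point therefore rests on the stated scoring rule, not on an omission.

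A reader might infer that the rule also sets the day 10, 20 and 30 TOTPAR to 100%. The text does not support this: the rule directly follows the sentence on the primary endpoint, those TOTPAR measures are secondary, and secondaries have their own exclude-or-impute rule. The wording is at most ambiguous.

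**Conclusion.** The point holds for days 4–5 of the primary endpoint. A deterministic best-case fill can set up to 40% of a patient's primary score (33% with day 0), under an undefined condition and with no confirmation of pain-free status. The size per affected patient, 16 to 4 points for R from 60 to 90, rests on assumed relief.

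Two stronger readings should be resisted. First, it is not true that non-response in general becomes the best result; the rule covers only diaries judged completed, with no relief entries after day 3. Second, a false-positive rate near 39% is not an expected value. It needs blank rates of 10% vs 30%, blanks unrelated to pain, and relief that stays at 60%. With rising relief the same blank rates give about 11%, and when blanks fall on patients with most relief the rate is about 3–5%, or about 9% at flat 60%. With equal rates the error stays near 5% and the loss of power is modest.

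The plan gives no blank rates or relief values with which to rule out the unfavourable cases, so the primary result should not depend on this fill alone.

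**What to change.** Amend {20c} before analysis:

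1. Define when a diary counts as completed.
2. In the primary analysis, score 100% only where the returned diary's own entries show complete relief or no pain.
3. Treat other blank day 4–5 pages as missing. Impute them with the MICE procedure already named, using days 0–3 relief, severe pain, analgesic intake, arm and stratification factors.
4. Keep the 100% fill as a prespecified sensitivity analysis beside a pessimistic one.
5. Report blank day 4–5 rates by arm.
6. State that the 100% rule does not apply to the day 10, 20 and 30 TOTPAR, which follow the secondary-endpoint rule.

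The cost is one paragraph of the plan and a few lines of R code, with no new patients or data. Intervals will be slightly wider. MICE may understate relief if patients stopped writing because pain had gone; the 100% sensitivity analysis covers that case.

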### Relevant concomitant care permitted or prohibited during the trial {11d}

Participants are provided with a standard pain treatment order including acetaminophen, ketoprofen, and weak opioids. They are allowed to use any additional medication or non-pharmacological pain relief, in such cases, this should be traced in the diary. In France, the access to non-steroid and opioid analgesics is highly regulated, so the chance that enrolled patients will considerably modify their home treatment is weak. Hypothetically, patients hospitalized during the follow-up period, or deceased, will be considered as lost for follow-up and therefore excluded.

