### Sample size {14}

In the beginning of our study, we were not able to identify any randomized study of educational intervention with TOTPAR as a primary endpoint. It has been reported, that more than 30% of orthopedic patients suffer from “important” pain (e.g., >6/10) during the first 72 h post-discharge [41, 42]. A 2-point change in the 11-item scale or 30% of the difference in pain intensity measurement is defined as clinically significant [43].

We analyzed the literature, reporting the effect of preoperative education on postoperative orthopedic pain in outpatient settings, and available on the year of the study development. Two studies reported the clinically significant effect from the preoperative education, with calculated OR 1.77 [95%CI 1.12–2.79] to 1.97 [95%CI 1.09–3.57] [44, 45]. However, the quality analysis of these studies demonstrated important heterogeneity, the absence of power calculation, small clinical effects, and design flaws.

As we were not able to find any relevant data for the sample size calculation, we have arbitrarily chosen the OR=2 from the effect of preoperative education, which will produce the decrease of proportion of patients with “important” pain from 30 to 17.6%. Giving this assumption, with the risk alpha of 5% and the power at 80%, allocation 1:1, the calculated sample size was 368 patients. We estimate the loss to follow-up at 10%, therefore the 410 patients will be finally enrolled.

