### Data collection and management

#### Plans for assessment and collection of outcomes {18a}

A dedicated electronic case report form (e-CRF) within Ennov Clinical® software was created and managed by Clinical Research Department, Hospices Civils de Lyon. The following data are collected upon inclusion: demographics, type of surgery, type of anesthesia, assessment of neuropathic pain with DN4, and assessment of the sleep quality with PSQI. After the discharge, patients fill in the dedicated diary. The prevalence of severe pain (which patients deem to be important) (binary), pain relief (continuous), painkiller administration (binary), and side effects from painkiller (binary) are collected in a time-dependent manner with 30 min grid over 24 h. On day 30, patients fill in the assessment of neuropathic pain with DN4, assessment of the sleep quality with PSQI, and the International Pain Outcome questionnaire (multiple binary, categorical and continuous variables). After the diary completion, patients were asked to send the collected data to the investigators.

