### Statistical methods

#### Statistical methods for primary and secondary outcomes {20a}

Analyses will be performed on an intention-to-treat basis. All data will be checked for normal distribution, and variables will be presented as mean ± standard deviation (SD) or as the median and interquartile range [IQR] accordingly. Categorical variables will be presented as the number and percentage of the total. To compare the two groups, we will use Fisher’s exact test for qualitative data and the non-parametric Mann-Whitney tests for quantitative variables. A comparison of the two groups at randomization will identify potential bias due to unequal allocation. A multivariate logistic regression analysis will be performed to study conditions independently associated with the response to the intervention and to control potential confounding factors. A 0.05 *p* value will indicate statistical significance. Statistical analyses will be performed using R software (R Foundation for Statistical Computing, Vienna, Austria).

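### Replacing randomised patients who lack early diary data contradicts the intention-to-treat basis stated for the primary analysis

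*Protocol article*

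**What the plan says.** All references are to the protocol article.

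- Section {20a} on statistical methods gives the analysis basis: "Analyses will be performed on an intention-to-treat basis".
- Section {20c} on missing data states: "No missing data will be accepted for the primary end-point". For gaps in the first three days after discharge, "patients will be replaced by new patients, recruited up to 186-target accrual". For a completed diary with no relief entries after day three, "the TOTPAR will be considered as 100% starting from the next blank page".
- Section {20c} offers multiple imputation by chained equations (MICE) for secondary endpoints only: "Missing data for the secondary endpoints will be examined and the decision guided by a principal investigator and statistician" settle whether those data are excluded or imputed.
- Section {11d} on concomitant care says that patients hospitalised during follow-up, or deceased, "will be considered as lost for follow-up and therefore excluded".
- Section {14} on sample size derives 368 patients and allows for attrition: "We estimate the loss to follow-up at 10" per cent, giving 410 to be enrolled. The abstract gives 414.

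**The concern.** Patients are randomised at the pre-anaesthesia visit ({26a}), before surgery. The diary begins after it. Whether a patient has diary data for days 1-3 is therefore known only after allocation, and it may depend on pain, sedation, readmission or engagement.

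Nobody is blinded ({17a}). The two arms receive different diary pages, and the intervention is meant to empower patients in managing their pain. Diary completion could plausibly differ between arms. If it does, and if patients without early data have different relief from those with it, the two analysed groups no longer differ by allocation alone.

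A new recruit who completes the diary does not repair this, because the new recruit passes through the same filter. More recruitment narrows the interval around a possibly biased estimate and leaves the bias in place. The report would also describe as intention-to-treat an analysis that is not. Section {20b} plans no additional analyses, so nothing stated would show how far the result depends on the missing patients.

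**Working it through.** **1. The plan's own sample size.** Inputs from {14}: 30% against 17.6% with important pain, alpha 5%, power 80%, 1:1. Sidedness is not stated; two-sided reproduces the figure. With pooled variance and no continuity correction,

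n per arm = [1.960 × √(2 × 0.238 × 0.762) + 0.842 × √(0.30 × 0.70 + 0.176 × 0.824)]² / 0.124² = (1.180 + 0.501)² / 0.01538 ≈ 184, so 368 in total, as stated.

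For 10% loss, 368 / 0.9 = 409, or 410 as an even number, as stated.

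**2. What 186 is.** The text gives it no unit. Odds of 0.30/0.70 halved give a rate of 0.1765 before rounding. The same formula then gives 186 per arm, 372 in total, and 372 / 0.9 = 414 after rounding up, which is the abstract's figure. So 186 reads as evaluable patients per arm. Read as a total (93 per arm), power at 30% against 17.6% would be Φ[(0.124 × √93 − 1.180) / 0.596] = Φ(0.03), about 51%, which cannot be intended.

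**3. Who reaches the primary analysis under the stated rules.**

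| Randomised patient | Stated handling | Section |
|---|---|---|
| Data for days 1-3, later blanks, diary completed | Kept, later relief set to 100% | {20c} |
| Missing data in days 1-3 | Replaced by a new recruit | {20c} |
| Hospitalised in follow-up or deceased | Excluded | {11d} |

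The second and third rows take randomised patients out because of something observed after allocation. That conflicts with {20a}. The restriction is to data for days 1-3, not to completeness over all five days.

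**4. Size of a possible bias.** Let m be the proportion lost in an arm, and let g be the shortfall in relief of lost patients against completers, taken as equal in both arms. In each arm, the mean over all randomised patients = completers' mean − m × g. Hence

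bias in the arm difference = g × (m in intervention − m in control).

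The documents give neither g nor loss by arm, so these values are assumptions, in points of percentage of maximum TOTPAR:

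| Difference in loss | g = 10 | g = 20 |
|---|---|---|
| 0 | 0 | 0 |
| 5 percentage points | 0.5 | 1.0 |
| 10 percentage points | 1.0 | 2.0 |

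With the planned 10% overall loss and 1:1 allocation, a 10-point difference means 5% in one arm and 15% in the other. The sign reverses if loss is higher in the control arm. If g differs between arms, equal loss no longer guarantees zero bias.

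**5. Is replacement needed for numbers?** At 10% loss, 410 enrolled leave 410 × 0.9 = 369 with data, against 368 required. For 414, 414 × 0.9 = 372.6 against 372. The planned inflation already covers the expected loss.

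**The case against.** The best defence has three parts. First, {20c} says replaced, not excluded, so in principle a replaced patient could still be analysed. Second, reminders, prepaid envelopes and a follow-up call from the coordinator ({11c}, {18b}) should keep loss low. Third, a fuller French protocol exists, and a statistical analysis plan may.

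The first part has limited force. Exclusion is an inference here, but the section accepts no missing primary data and reserves MICE for secondary endpoints, so it leaves a replaced patient no route into the primary analysis. In {11d} the exclusion is explicit. The second part bears on how large the bias is, not on whether the rule conflicts with {20a}; {11d} itself presents hospitalisation and death as hypothetical. The third does not remove a conflict between two current statements.

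Several stronger readings are tempting, but the documents do not support them:

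- *One empty half-hour entry triggers replacement.* Relief data "are collected in a time-dependent manner with 30 min grid over 24 h", but {20c} speaks of blankness only by the page. TOTPAR is an area under a curve from repeated assessments and does not need every half-hour filled.
- *Losses are allowed for twice, or enrolment is open-ended.* The rule names a target. Replacement up to 186 evaluable per arm may simply be how the 10% allowance is used. What can be said is that the unit of 186 and its relation to 410 and 414 are not stated.
- *Patients have already been replaced.* The trial status section reports only that 256 were recruited.
- *The bias is known to be large.* No per-arm loss, relief gap or TOTPAR standard deviation is given.

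**Conclusion.** The contradiction stands and should be resolved before the arms are compared. Followed as written, the plan gives a primary analysis of patients with data for days 1-3, less those hospitalised or deceased. It does not give the intention-to-treat analysis it promises.

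This conclusion rests on the text alone, together with the reading that a replaced patient has no place in the primary analysis. The size and direction of the bias remain unknown. The range of 0.5-2 points is an illustration under assumed loss differences and relief gaps, and zero is possible. Since no TOTPAR standard deviation is stated, this range cannot be set against a detectable difference without a further assumption.

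**What to change.** - Delete the replacement rule in {20c} and, for the primary analysis, the exclusion in {11d}. Analyse every randomised patient in the allocated arm, including any who has been replaced by then.
- Extend MICE, already named for secondary endpoints, to missing primary TOTPAR. Use arm, the stratification factors (type of surgery and of anaesthesia), baseline PSQI and DN4, and any observed diary days.
- Add a delta (tipping-point) sensitivity analysis, and amend {20b} to match. It is needed because imputation adds little for a diary that was never returned: with only baseline data to draw on, the result may stay close to that from observed cases.
- Stop at a fixed enrolment with the 10% allowance included. State the unit of 186 and reconcile it with 368 and 410 in {14} and 414 in the abstract. The first and last follow from the unrounded rate, the middle two from the rounded one.

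The cost is protocol and analysis-plan wording, imputation code, and a modest loss of precision compared with a full set of completers. No increase in planned enrolment is needed. No interim analysis is planned, and 256 patients had been recruited when the article was revised. At that point the change could be made through the amendment route in {25} before any planned comparison of the arms.
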